## Methods

### Aim

The aim of this study will be to determine whether patients who are treated with the IHSS model will have improved treatment satisfaction (increase of 10% over pre-intervention rates), improved treatment completion (increase of 10% over pre-intervention rates), and a greater reduction in health system usage (substance use related presentations to emergency room and hospital admissions) at one-year follow-up compared to those treated within the abstinence-based model (decrease of 10% over pre-intervention rate).

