### Design

We will conduct a pre/post Quasi Experimental Community trial in northern Ontario, Canada, comparing historical treatment outcomes for past Benbowopka patients to outcomes following the implementation of IHSS treatment for Indigenous patients with a history of IGT and SUD. We will conduct a quantitative and qualitative analysis to understand the differences before and after the intervention is implemented. The pre-IHSS intervention study window will span over 36 months (April 1, 2013–March 31, 2016; *n* = 343), and the post-IHSS intervention study window will span the 27 months post-IHSS implementation (January 1, 2018–March 31, 2020; *n* > 300). We conducted an a-priori sample size calculation for our study with an anticipated effect size of 0.5, and probability level of 0.05. To have appropriate statistical power of > 80%, we would need 65 patients in each group. With the anticipated sample sizes of 300 pre and post-implementation, we have enough statistical power to confidently evaluate our outcomes.

All patient data will be anonymized at the time of data entry. Propensity score matching will be undertaken to evaluate the association between the IHSS treatment and long-term outcomes. The National Native Alcohol and Drug Abuse Program (NNADAP) tool will be used to analyze the program objective; that is, whether completion rates improve following the implementation of the IHSS intervention. Additionally, a Client Quality Assurance Survey will be utilized to determine patient satisfaction.

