### Propensity score matching

Logistic regression will be used to define propensity scores for treatment groups (pre and post intervention). The treatment group will be matched 1:1 to control using a caliper width of 0.20 greedy matching [54]. Standardized differences (d) will be calculated for each covariate before and after matching. Standardized difference (d) less than 0.10 will indicate balanced covariates [55]. Propensity score matched data will be analyzed to calculate the effect of receiving treatment post-intervention on each helth system usage outcome using McNemar’s test [56]. Proportions will be used to calculate clinical descriptors including relative risk (RR) and number needed to treat or number needed to harm (NNT/NNH), along with 95% confidence intervals (CI) for each descriptor calculated. All statistical analysis will be conducted on the remote server using SAS Version 9.4 [57]. Data will be reviewed by ICES to insure privacy standards are met.

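### The power statement is built on a standardized effect of 0.5, which does not correspond to the 10% changes in rates that the Aim sets as targets

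*Protocol article*

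**What the plan says.** The Design section gives the sample-size basis as "an anticipated effect size of 0.5, and probability level of 0.05", with more than 80% power. It names no outcome, unit or test for this effect. It then says "we would need 65 patients in each group. With the anticipated sample sizes of 300 pre and post-implementation, we have enough statistical power" to evaluate the outcomes with confidence.

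The Aim section states the targets as changes in rates. One is "improved treatment completion (increase of 10% over pre-intervention rates"; satisfaction has the same 10% increase, and substance-use-related health-system use has a 10% decrease at one year. The Data analysis section makes these three the primary outcomes.

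The Data collection section records completion as yes or no. For usage, the Propensity score matching section says "Propensity score matched data will be analyzed to calculate the effect of receiving treatment post-intervention on each helth system usage outcome", using McNemar's test after 1:1 matching, with relative risks and numbers needed to treat. Completion is therefore binary, and usage is to be compared as proportions.

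**The concern.** A power statement should concern the effect the study is designed to find. Here the Aim speaks of 10% changes in rates while the calculation uses a standardized effect of 0.5, and nothing in the article connects the two. If 0.5 is much larger than the stated target, the number needed is understated, and the margin of 300 over 65 says nothing about power for that target.

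What is at stake is the reading of a null result. A reader who accepts the claim of ample power would take a non-significant primary outcome as evidence that the new programme brings no benefit. The design could instead have missed an improvement of exactly the size it set out to detect.

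**Working it through.** **Inputs from the article.** Effect 0.5; probability level 0.05, sidedness not stated; power above 80%; 65 per group needed; 300 per period anticipated (all from Design). Target of 10% up or down (Aim), without saying whether this means percentage points or relative change. No baseline rate is given for any outcome, so baselines are assumed over a range.

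**Reproducing 65.** For two means with standardized difference d, n per group = 2(z₀.₉₇₅ + z₀.₈₀)²/d² = 2(1.960 + 0.842)²/0.25 = 62.8, so 63. The exact t-test gives 64, and 65 per group has 80.8% power. A one-sided test would need only 50, so the figure is two-sided. The arithmetic is right for d = 0.5.

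**What 0.5 means for a proportion.** With Cohen's h = 2·arcsin√p₂ − 2·arcsin√p₁, h = 0.5 from 60% is a rise to about 82%. From baselines of 30–70% it is a rise of about 20 to 25 points. A 10-point rise from 40–70% is only h ≈ 0.20–0.23, and a 10% relative rise from the same baselines is h ≈ 0.08–0.16.

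**Sample size for the stated target.** Pooled two-proportion formula, two-sided 0.05, 80% power, with p̄ the mean of p₁ and p₂:

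n = [1.960·√(2p̄(1−p̄)) + 0.842·√(p₁(1−p₁) + p₂(1−p₂))]² / (p₁−p₂)²

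Example, 60% to 70%: (1.322 + 0.565)²/0.01 ≈ 356 per group. Power at 300: Φ[(0.10·√300 − 1.322)/0.671] = Φ(0.611) = 73%.

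| Assumed pre-period rate | +10 points: n for 80% | power at 65 | power at 300 | +10% relative: n for 80% | power at 300 |
|---|---|---|---|---|---|
| 20% | 294 | 26% | 81% | 6510 | 9% |
| 30% | 356 | 22% | 73% | 3763 | 12% |
| 40% | 388 | 21% | 69% | 2389 | 17% |
| 50% | 388 | 21% | 69% | 1565 | 23% |
| 60% | 356 | 22% | 73% | 1016 | 33% |
| 70% | 294 | 26% | 81% | 623 | 49% |
| 80% | 199 | 36% | 93% | 329 | 76% |

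For a fall in usage, taken as the proportion with any such use, at 300 per group:

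| Assumed pre-period rate | power, −10 points | power, −10% relative |
|---|---|---|
| 20% | 93% | 9% |
| 30% | 81% | 13% |
| 40% | 73% | 17% |
| 50% | 69% | 23% |
| 80% | 81% | 63% |

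McNemar's test on 300 pairs with uncorrelated members gives nearly the same values: 69% for 50% to 40%, and 23% for 50% to 45%.

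**Does 65 ever suffice?** Over a grid of baselines in half-point steps, on both readings and in both directions, the smallest two-sided requirement was 81 per group.

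**When does 300 suffice?** For +10 points, power is below 80% for baselines of about 21–69%. For −10 points, it is below 80% for about 31–79%. For +10% relative, it reaches 80% only above about 81%; for −10% relative, only above about 86%.

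**The case against.** The strongest reply is that 65 is correct for the effect entered, and that the sample comes from fixed calendar windows at one centre rather than from this calculation. The full protocol may say which outcome the 0.5 belongs to. Satisfaction comes from a survey whose scoring is not shown; if it is a scale score, a standardized 0.5 could apply to it, although the Aim's word for it is rates. All of this is fair. None of it ties 0.5 to a 10% change in completion or usage, yet the claim of adequate power is made for the outcomes as a whole.

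Three stronger readings are tempting and should not be drawn.

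- A reader might infer that 65 is a miscalculation. It is not; the fault is the choice of effect.
- A reader might infer that 300 per group is far too few in most plausible cases. That holds only if 10% is relative. On the percentage-point reading, power is modestly below 80% in the middle of the range and at or above 80% outside it. With 343 and 300 unmatched, a rise from 60% to 70% has about 76% power and from 70% to 80% about 83%.
- A reader might infer that far fewer than 300 will be analysed, since 27 months at about 90 patients a year gives 27/12 × 90 ≈ 203. The article states more than 300 for the post period, and its Setting section ends that window in March 2021, which is 39 months or about 293 at the same rate. The conflict over the window needs its own resolution and cannot be settled here by taking the lowest figure. Matched-pair analysis is also specified only for the usage outcomes, so a matched number should not be imposed on completion or satisfaction.

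**Conclusion.** The point stands as a mismatch between the effect used for sizing and the stated targets. For proportions, 65 per group gives about 21–36% power for a 10-point rise (baselines 10–80%) and about 7–24% for a 10% relative rise (baselines 40–80%), so it is too few for the Aim. The inference from 300 exceeding 65 to adequate power therefore fails.

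The article does not allow a firm statement on whether 300 is itself too few. That depends on the unstated baselines and on whether 10% is absolute or relative. The figures assume a two-sided 0.05 test, binary outcomes, equal groups of 300 and, for the usage pairs, little correlation within pairs.

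**What to change.** Replace the effect-size-0.5 statement in the Design section:

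- Say for each primary outcome whether 10% means percentage points or relative change.
- Take the pre-period rates from the centre's historical records, which the Data collection section already plans to extract.
- Report power or minimum detectable difference per primary outcome on the number actually analysed: matched pairs for health-system usage, and the applicable sample for completion and satisfaction. As an illustration, from a 60% baseline with 300 per group the minimum detectable rise at 80% power is about 10.9 points.
- If satisfaction is a scale score, say so and give its own effect size.
- Delete the requirement of 65 per group and the unqualified claim of enough power.

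The cost is a rewritten paragraph and a short recalculation. No extra enrolment is needed, but the stated power will look less favourable.

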**Methods:**

We will conduct a pre/post Quasi Experimental Community trial, to compare historical treatment outcomes for patients following the implementation of Indigenous Healing and Seeking Safety. We will conduct quantitative and qualitative analyses to understand the differences before and after the intervention is implemented. The pre- Indigenous Healing and Seeking Safety intervention study window will span from 2013 to 2016; *n* = 343, and the post-Indigenous Healing and Seeking Safety intervention study window from 2018 to 2020; *n* > 300. All participants will be enrolled in the Benbowopka residential treatment for the first time during the study periods. All data will be anonymized at the time of data entry. Propensity matching will be undertaken for patient characteristics, including sex/gender, age, and substance use type.

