The abstinence model of service that was being delivered at Benbowopka Treatment Centre was excluding many individuals who were seeking residential addictions treatment for problems related to prescription opioids and other drugs. Individuals who were on prescribed medication, including opioid agonist treatment, by their physician to address SUD or mental health challenges were not eligible for admission to Benbowopka Treatment Centre because of its abstinence-based model of service. In 2014, Mamaweswen North Shore Tribal Council directed Benbowopka Treatment Centre to move forward with a plan for the realignment of its services to a harm reduction model of service that would follow the best practice strategies recommended for addictions treatment. Thus, the implementation of the Indigenous Healing and Seeking Safety (IHSS) approach at Benbowopka for Indigenous patients with a history of IGT and SUD was initiated in 2016.

The Mamaweswen (North Shore Tribal Council) and the Benbowopka Treatment Centre represent seven member communities (Batchewana, Garden River, Thessalon, Sagamok, Mississauga, Atikameksheng, and Serpent River) on the North Shore of Lake Huron. Benbowopka treats approximately 90 patients per year in a residential treatment program. The program has high-quality retrospective data based on standardized assessment screening tools routinely used by the Drug and Alcohol Treatment Information System and the National Native Alcohol and Drug Abuse Program.

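### The power assurance from 300 patients per period does not carry over to the health-system primary outcome, which is tested in matched pairs against a 10% target

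*Protocol article*

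**What the plan says.** In the protocol article, Design, the sample-size basis is: "We conducted an a-priori sample size calculation for our study with an anticipated effect size of 0.5, and probability level of 0.05". The result is: "To have appropriate statistical power of > 80%, we would need 65 patients in each group". The conclusion follows: "With the anticipated sample sizes of 300 pre and post-implementation, we have enough statistical power to confidently evaluate our outcomes". It makes no exception for any outcome and gives no numerical power at 300. The same section gives the earlier period as "April 1, 2013–March 31, 2016; *n* = 343" and expects more than 300 patients in the later one.

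Under Propensity score matching, the health-system outcomes are handled differently: "The treatment group will be matched 1:1 to control using a caliper width of 0.20 greedy matching". Each of these outcomes is then tested with McNemar's test in the matched data. The abstract names the characteristics: "Propensity matching will be undertaken for patient characteristics, including sex/gender, age, and substance use type". The Data analysis section makes health-system use in the year after treatment one of three primary outcomes, and the Aim section sets its target as a 10% decrease from the earlier period.

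**The concern.** The sample size in the power sentence is not the one used for the health-system outcome. Only matched pairs enter McNemar's test, and the sample-size text does not allow for unmatched patients. There is little reserve, with 343 controls for just over 300 treated patients.

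The article also gives reason to expect imperfect overlap. Its Background says that the earlier abstinence model "was excluding many individuals who were seeking residential addictions treatment for problems related to prescription opioids and other drugs", one objective is to learn whether a broader range of people is now served, and substance type is a matching characteristic.

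The effect size matters as well. The assurance rests on 0.5, while the target for this outcome is 10%. If the study finds no difference in emergency visits or admissions, readers will rely on the power sentence to interpret that result.

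**Working it through.** **Step 1: reproduce the plan's figure.** Inputs from Design: effect size 0.5 (read as a standardised mean difference), alpha 0.05 (taken as two-sided), power 80%.

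n per group = 2(1.960 + 0.842)² / 0.5² = 62.8, so 63; the t-test version gives 64. Power at 65 per group is 0.813 (normal) or 0.808 (t). The stated 65 with more than 80% power is reproduced.

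**Step 2: matching loss at effect size 0.5.** Power = Φ(0.5√(n/2) − 1.960). At n = 150 this is Φ(4.330 − 1.960) = 0.991. McNemar's test with a binary effect of the same size (arcsine scale, h = 0.5, base rates 20% to 60%, uncorrelated pairs) gives 0.98 to 0.99 at 150 pairs. Matching would have to discard (300 − 65)/300 = 78% of 300 before the number fell to 65.

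**Step 3: how many pairs.** The number of pairs cannot exceed the smaller group. The article gives no case mix or match rate, so the yield was simulated: 343 earlier and 300 later patients, propensity model on sex, age and four substance classes, greedy 1:1 matching without replacement, caliper 0.2 SD of the logit (the article gives no unit), 200 runs per scenario. All mixes are assumptions.

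| Assumed change between periods | Pairs (about) |
|---|---|
| None | 286 |
| Opioids 20% to 35% | 260 |
| Opioids 20% to 45%, mean age 3 years lower | 226 |
| Opioids 10% to 50%, mean age 3 years lower | 181 |

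**Step 4: McNemar power at the 10% target.** With m pairs, rates p1 and p2 and uncorrelated pairs, let d = p1 − p2 and pd = p1(1 − p2) + p2(1 − p1). Then

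power = Φ[(d√m − 1.960√pd) / √(pd − d²)].

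For 30% against 20%: pd = 0.24 + 0.14 = 0.38 and √(pd − d²) = √0.37 = 0.608.
- m = 300: (1.732 − 1.208)/0.608 = 0.861, power 0.81.
- m = 181: (1.345 − 1.208)/0.608 = 0.225, power 0.59.

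The base rates are assumed. Results for an absolute fall of 10 points:

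| Rates | 300 pairs | 260 pairs | 181 pairs |
|---|---|---|---|
| 20% vs 10% | 93% | 89% | 76% |
| 30% vs 20% | 81% | 75% | 59% |
| 50% vs 40% | 69% | 63% | 48% |
| 30% vs 20%, within-pair correlation 0.2 | 88% | 83% | 68% |

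For a relative fall of 10% (uncorrelated pairs, 300 pairs): 30% vs 27% gives 13%, 40% vs 36% gives 17%, and 50% vs 45% gives 23%.

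**Step 5: why 0.5 and 10% differ.** On the arcsine scale, a 10-point fall from base rates of 20% to 70% is h = 0.20 to 0.28, about half the effect size used in the plan. That is the range in which having 300 pairs or 180 makes a difference.

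**The case against.** The strongest reply is that nothing stated in Design is overturned. It gives no power at 300. It says that 65 per group give more than 80% at effect size 0.5 and presents 300 as a margin. Even the lowest simulated yield, 181 pairs, is 2.8 times 65. This stands: a reader might infer that matching alone brings power below the stated level, and on the plan's own effect size it does not. The matching point therefore has force only together with the 10% target.

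Three further limits also stand.
- The size of the loss is not known. With no change in case mix about 286 pairs remain, and the larger losses come from assumed mixes. The ceiling may lie somewhat above 300, since more than 300 later patients are expected.
- A reader might infer that the later patients dropped are mainly those the new programme newly admits. The assumed mixes produce that result, but the article does not establish it. Matching is on a single score, so a patient can be paired with someone who used another substance. The stated ineligibility rule concerned prescribed medication, which is not among the matching characteristics the abstract names.
- Matching is tied to long-term and health-system outcomes. Nothing confines completion or satisfaction to matched pairs.

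It can also be said that expected match yield belongs in the full protocol or analysis plan. That is fair for the detail. It does not cover a conclusion that the article itself draws for all its outcomes from a number that one primary outcome does not use.

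**Conclusion.** The assurance of enough power is not supported for the health-system primary outcome at the plan's own 10% target with the pairs actually analysed.

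On the absolute reading the answer depends on the base rate. At 20% vs 10%, power stays above 80% unless pairs fall to about 200. At 30% vs 20%, it is just adequate at 300 pairs and inadequate below that if pairs are uncorrelated; a within-pair correlation of 0.2 keeps it at 80% down to about 240 pairs. At 50% vs 40%, it is short even at 300. On the relative reading, power is far too low before any pair is lost, so the effect size rather than matching is the cause.

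These figures rest on assumed base rates, assumed case mixes, a two-sided 0.05 level and the normal approximation. The calculation of 65 per group at effect size 0.5 is correct as far as it goes.

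**What to change.** In Design, limit the present sentence to an effect size of 0.5. For the health-system outcome, add the McNemar power at the expected number of matched pairs, given as a range, for the target in the Aim section. State whether 10% is absolute or relative, and give the base rate and within-pair correlation assumed.

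Under Propensity score matching, commit to reporting how many later-period patients the caliper leaves unmatched, and their substance type, so that readers can see whom the estimate describes.

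A weighted analysis that retains all patients is an optional sensitivity analysis. Overlap weighting would change the estimand and give less weight to the patients with poor overlap, so this should be stated if it is used.

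The cost is wording and a short calculation, and the stated power becomes less favourable. No extra patients or data are needed.

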### Setting of the study

Benbowopka treats approximately 90 patients per year in a residential addiction treatment program in Blind River Northern Ontario. The study periods will include pre-intervention (April 1, 2013–March 31, 2016) and the post-IHSS intervention study window spanning the 27 months post-IHSS implementation (January 1, 2018–March 31, 2021; *n* > 300). Time periods will be chosen to allow analysis by both calendar year and fiscal year. On every 28-day treatment cycle, participants will be recruited and informed by the staff at Benbowopka about the study and, if interested, a consent will be obtained. The data collection will include data from patients initiating treatment at Benbowopka during the study window. Patient follow-up will occur in the year following treatment completion and/or discontinuation. Anonymized patient records will be linked via Ontario Health Insurance Plan (OHIP) number to the administrative health data at the ICES. ICES, formally known as the Institute for Clinical Evaluative Sciences, is an independent research institute that collects and analyzes data on publicly funded health services for research. The data will be queried in the one year following completion or discontinuation of IHSS at Benbowopka to ascertain the impact of substance use on health outcomes including hospitalization, emergency department visits and opioid-related overdose. For patients with multiple admissions, the date of first admission will serve as the index date for health outcomes evaluation.

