### Study population

We will only include data from first-time patients initiating treatment at Benbowopka, meaning that there will be no previous history of treatment at this center. It is common for patients to cycle between treatment and relapse. Studies have shown that multiple treatment attempts are associated with a higher likelihood of positive outcome [32]. Therefore, we will only include first-time patients to eliminate bias associated with cases involving multiple treatment attempts.

Benbowopka’s residential treatment program collects individual-level data based on standardized assessment screening tools routinely used by the Drug and Alcohol Treatment Information System and the National Native Alcohol and Drug Abuse Program. The cohort for this study will be created by using anonymized patient records from the Ontario Health Insurance Plan (OHIP) number. We will link the OHIP number to the administrative health data at ICES in order to be able to evaluate broad health outcomes for patients after they completed the treatment program. ICES routinely links partner data to its core health systems data holdings. We will then query data in the one year following completion or discontinuation of IHSS at Benbowopka to ascertain *Impact of Substance Use on Hospital Costs* as defined by the Canadian Center on Substance Abuse [42]. ICES linkage will enable virtual follow-up of Benbowopka patients for health systems usage. A detailed timeline can be found in the appendix.

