### Data collection

The historical program data will be collected from Benbowopka’s records from January 2013 to March 2016 (end of the 2015 fiscal year). The data will be divided into fiscal year and intake period at the request of Benbowopka. Historical demographic data for each intake period will be found in the “Client Information Summary” folders in Benbowopka’s archive room.

We will use the Drug Use Screening Inventory (DUSI) to collect data on patients during the program. The DUSI and a revised version (DUSI-R) were developed by the Center for Addiction and Mental Health (CAMH) to identify consequences of alcohol and drug involvement [49]. The DUSI is a 149-item multidimensional instrument that quantifies not only involvement with drugs and alcohol, but also associated problems in the areas of mental health and psychosocial domains. The DUSI-R consists of 159 items. The following variables will be collected: name, health card number, date of birth, postal code, status card number, gender, date of admission to the program, date of discharge, program completion (Y/N), Indigenous (Y/N), status First Nation (Y/N), on reserve (Y/N), primary substance, and secondary substance(s). Drug classes from primary and secondary substances will be further divided into a sub-substance category. Any pertinent notes will also be included in the data.

The original data will include drug classes used by Benbowopka (i.e. alcohol, narcotics, prescription drugs, solvents/inhalants, and other). The revised data will be organized by the drug class preference of the research team (i.e. alcohol, cannabis, stimulants, opioids, depressants, hallucinogens, inhalants/solvents). Some drug names will be changed to ensure cohesion (e.g. brand to generic names, acid to LSD, etc.).

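### Opt-in consent in the post-IHSS period is not reconciled with the records-based cohort; if consent decides inclusion, the two periods enter patients differently and completion may be biased

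*Protocol article*

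**What the plan says.** Three sections of the protocol article describe how patients enter the data.

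- **Setting of the study**, on each treatment cycle: "participants will be recruited and informed by the staff at Benbowopka about the study and, if interested, a consent will be obtained". The next sentence has no consent qualifier: "The data collection will include data from patients initiating treatment at Benbowopka during the study window".
- **Study population**: "The cohort for this study will be created by using anonymized patient records from the Ontario Health Insurance Plan (OHIP) number". The same section limits the study to new patients: "We will only include data from first-time patients initiating treatment at Benbowopka".
- **Data collection**, for the pre-IHSS period: "The historical program data will be collected from Benbowopka", from "records from January 2013 to March 2016 (end of the 2015 fiscal year". No consent step is described. The variables listed there include completion (yes/no) and the admission and discharge dates.

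Program completion is one of three primary outcomes (Data analysis). The Aim sets a 10% increase over the pre-intervention rate as the target, without saying whether that is absolute or relative. The Abstract names sex/gender, age and substance use type as matching variables. The Propensity score matching section applies the matched analysis to the health-system usage outcomes.

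**The concern.** In a pre/post comparison with historical controls, the rule that admits a patient to the data has to be the same in both periods. Here one period is described with staff recruitment and opt-in consent, and the other with archive retrieval.

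Suppose only consenting patients enter the post-IHSS data. Patients who leave early in a 28-day stay, or who are less engaged, may be approached less often or agree less often, and such patients would be over-represented among non-completers. Dropping them from one period only would move the observed completion rate with no change in treatment. Health-system use in the following year could be affected in the same way.

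Matching would not repair this. Age, sex/gender and substance type do not capture willingness to take part, and patients who never enter the data cannot be matched. The article's limitations paragraph does not mention selection.

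**Working it through.** **1. The plan's own figure.** The Design section asks for 65 patients per group at effect size 0.5, significance level 0.05 and power above 80%. The two-sided normal approximation gives 63, the t-test gives 64, and power at 65 is 0.81. The figure reproduces, but it has no bearing here: sample size does not remove selection bias.

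**2. What the text supports.** Read alone, the recruitment sentence concerns consent to the study as a whole. It stands between the study windows and the sentences on data collection and record linkage. The sentence after it, and the Study population section, describe a cohort built from records. No sentence says that non-consenters' records are excluded, and none says that they are kept.

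**3. Does the sample size settle it?** The post-IHSS sample is stated as more than 300. The Setting section says "Benbowopka treats approximately 90 patients per year in a residential addiction treatment program". The post window is 27 months by the Design section's dates and 39 months by the Setting section's dates.

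- At 90 per year: 90 × 27/12 ≈ 203, or 90 × 39/12 ≈ 293. Both are below 300 even with full inclusion.
- At the historical pace of 343 in 36 months: 343/36 × 27 ≈ 257, or 343/36 × 39 ≈ 372.
- A consent-only cohort could exceed 300 only at the historical pace over 39 months, and only with overall consent above 300/372 ≈ 81%.

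The stated size therefore fits an all-records cohort better, but it does not exclude the other reading.

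**4. Size of the bias if consent decides inclusion.** The documents give no completion rate and no consent rate, so these are assumptions. Let p be the true completion rate, equal in both periods, and let c1 and c0 be the consent probabilities of eventual completers and non-completers. Then

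observed post-period completion = p·c1 / (p·c1 + (1 − p)·c0).

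Example: p = 0.70, c1 = 0.90, c0 = 0.70 gives 0.63 / (0.63 + 0.21) = 0.750, a bias of +5.0 points.

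Bias in percentage points:

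| Consent, completers vs non-completers | p = 50% | p = 60% | p = 70% | p = 80% |
|---|---|---|---|---|
| 70% vs 90% | −6.3 | −6.2 | −5.5 | −4.3 |
| 90% vs 90% | 0 | 0 | 0 | 0 |
| 90% vs 80% | +2.9 | +2.8 | +2.4 | +1.8 |
| 90% vs 70% | +6.3 | +5.9 | +5.0 | +3.7 |
| 90% vs 50% | +14.3 | +13.0 | +10.8 | +7.8 |
| Target if 10% is absolute | 10 | 10 | 10 | 10 |
| Target if 10% is relative (0.10 × p) | 5 | 6 | 7 | 8 |

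At 90% vs 70%, the artefact is 37% to 63% of an absolute target. Against a relative target it runs from just under half (3.7 of 8 points) to more than all of it (6.3 of 5). At 90% vs 50% it exceeds the absolute target for completion of 50% to 70%.

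No corresponding figure is computed for health-system use, because the documents give no event rates.

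**The case against.** The strongest reply is that consent may not govern the quantitative data at all. The study also includes interviews and Sharing Circles, which would need individual consent, and the recruitment sentence may refer to those. The Study population section builds the cohort from records, and the stated sample size fits that better. This stands as a possible reading. It does not dispose of the point, because the consent sentence is worded for the study as a whole and the article leaves the two descriptions side by side.

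A reader might infer something stronger: that the post-IHSS cohort consists of volunteers, the historical cohort is everyone in the archive, and the IHSS results are therefore inflated. The documents do not support this, for three reasons.

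- Exclusion of non-consenters is nowhere stated. The absence of a pre-period consent step is only silence in a condensed article.
- The restriction to first-time patients applies to both periods, so the historical cohort is not the whole archive.
- The direction is not established. The article does not say when in the cycle consent is sought or how many agree. If consent is sought at intake, early leavers may be approached too. The bias is zero if consent is unrelated to completion and negative if completers consent less often.

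The article also keeps patients who discontinue: "Patient follow-up will occur in the year following treatment completion and/or discontinuation". That protects against losing discontinuers who are already in the data, but not against missing those never enrolled.

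Nor should the completion argument be carried over to satisfaction. That outcome comes from a survey, which may have its own response selection in either period.

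**Conclusion.** The point holds conditionally. The article describes opt-in consent for the post-IHSS period and archive retrieval for the pre-IHSS period, and it does not reconcile the first with its own records-based cohort. If consent determines inclusion, entry is asymmetric and the named matching variables would not correct it. The comparisons of completion and health-system use may then be biased. Favouring IHSS is the more plausible direction, because early leavers have less opportunity to be enrolled, but it is not certain.

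The range of about −6 to +14 points on completion rests wholly on assumed values: completion of 50% to 80%, consent of 50% to 90%, and no true effect. It shows that plausible consent patterns could produce a change as large as the 10% target. It does not estimate what will happen. If inclusion does not depend on consent, this bias does not arise and only the wording needs correcting.

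**What to change.** State whether consent determines inclusion in the post-period quantitative data. Then define that cohort identically in both windows as all first-time admissions, with completion and the admission and discharge dates taken from the routine program record, where ethics approval, OCAP and community governance permit. Limit individual consent to interviews, Sharing Circles and study-specific data.

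Where governance requires individual consent for post-period data or linkage:

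- report the fraction of eligible first-time admissions who consented;
- report the aggregate completion rate of those who did not;
- add a sensitivity analysis that weights consenters on baseline data. Such weighting corrects only for selection related to the measured variables, so the aggregate completion of non-consenters remains the more direct check.

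The cost is some consultation with the ethics board, the Tribal Council and the Chiefs of Ontario, plus a little extra analysis. The completion variables are already listed in the Data collection section, so no new data collection is needed.
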